**3.3 Exclusion criteria**

The exclusion criteria will:

1. Patients who are pregnant or breast feeding
2. Patients who are not undergoing contraceptive treatments
3. Patients who have taken antibiotics and/or probiotics within the previous 3 months
4. Patients who have had a positive glucose breath test in the past
5. Patients with an organic colonic or anorectal disease (cancer, ischemia, infection, etc.)
6. Patients with an autonomic diabetic neuropathy, dysthyroidism, coeliac disease, or connective tissue disease
7. Patients who have undergone intestinal surgery (except cholecystectomy or appendectomy)
8. Patients with a psychiatric disorder
9. Patients who have participated in another medicinal product study during the 30 days preceding the inclusion visit
10. Patients who are allergic to metronidazole
11. Patients who do not speak or read French
12. Patients who are no longer autonomous

Patients who are taking a treatment (laxative, anti-diarrheic treatment, morphine, antidepressant, etc.) that may interfere with their gastro-intestinal motility or sensitivity will be asked to continue their treatment during the study. In the event of a significant change during the study, the patient will be excluded.

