If a patient displays secondary effects or develops an allergy to metronidazole or Carbosylane^®^, he/she will be excluded from the study and will be replaced by another patient. Given the number of patients that will potentially be excluded from the study following their inclusion, we plan on recruiting 50 patients in order to maintain a 20-patient cohort for each experimental arm (Carbosylane^®^ and metronidazole).

The main primary outcome will be the percentage decrease in the mean daily number of gas leakages reported in the 3-day diaries that will be completed before (baseline) and at the end of the 10-day treatment period and before the regimen performed prior to the glucose breath test. A positive clinical response will be defined as a greater than 50% reduction in the mean daily number of gas leakages.

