**4. DATA ANALYSIS AND STATISTICS**

**4.1 Number of patients**

Due to the lack of a preliminary study on the efficacy of treatments for flatus incontinence, we were unable to determine a sample size and decided to arbitrarily enroll 20 patients in each group for the pilot study.

To maintain 20 patients in each experimental arm (i.e., 20 patients treated with Carbosylane^®^ and 20 with metronidazole), we plan to recruit 25 patients for each experimental arm to compensate for non-compliant patients and patients who develop allergies or intolerance to treatment, or who are lost at follow-up. The frequency of positive glucose breath tests in patients with flatus incontinence is difficult to estimate because this has never been investigated. However, we presume that one out of three patients will have a positive glucose breath test.

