**4.2 Data collection**

**Demographic data, clinical symptoms**: All the data will be collected and will be compiled in individual patient case report forms (CRFs), which will be archived in the investigation center. Information will be collected by the research staff or the investigator from the patient and from his/her medical record.

**Bowel diary**: Three-day bowel diaries describing flatus incontinence episodes (main criterion), bowel movements, urgency episodes, and fecal incontinence episodes will be completed by each patient. The treatment and the secondary effects will be noted in the diaries. The bowel diaries will be completed at the beginning of the study before the treatments and at the end of the treatments.

**Fecal incontinence severity score**: The Cleveland Clinic score will be used (Jorge, 1993). Scores will be recorded at the beginning and at the end of the study.

**Quality of life scores**: Quality of life will be evaluated using two questionnaires that have been validated in French. One is specific for fecal incontinence (FIQL) [Rullier, 2004] while the other is specific for functional digestive disorders (GIQLI) [Slim, 1999]. These questionnaires will be completed at the beginning and at the end of the study.

**Symptom scores**: The patients will be asked to subjectively rate the intensity of each symptom (bloating, abdominal pain, borborygmi) using the following scores: 0 = none, 1 = mild, 2 = moderate, and 3 = severe. The means of the scores attributed daily for 3 days will be calculated to obtain the final scores for the symptoms at the beginning and at the end of the study.

**Treatment compliance**: Treatment compliance will be evaluated by counting the number of tablets remaining at the end of the study.

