**4.3 Data analysis**

Results will be expressed as means ± standard deviation. The mean number of flatus incontinence episodes during the 3 days prior to and at the end of the treatment will be calculated. The difference between the mean number of flatus incontinence episodes before and during the treatment and the percentage decrease in the mean daily number of flatus incontinence episodes will be calculated and will compared between the two groups of patients (metronidazole and Carbosylane^®^ groups). The severity scores, quality of life scores, mean number of bowel movements, fecal incontinence episodes, urgency episodes, and symptomatic scores will be compared between the two groups.

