**7.5 Expected serious adverse events**

There are no expected serious adverse events related to the glucose breath test. Metronidazole could cause the following serious adverse events: digestive disorders, glossitis, pancreatitis (rare), pruritus, cutaneous eruptions, anaphylactic shock, neuropathy, vertigo, headaches, convulsions, confusion, and hematological disorders. These serious adverse events will be declared using the methodology described in the previous section.

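### Section 3.6 excludes and replaces randomised patients who react to their drug, so the primary comparison would most naturally cover only patients who tolerated it

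*Protocol*

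**What the plan says.** Under section 3.6, patients with a positive breath test complete a 3-day diary, are randomised, and take metronidazole or Carbosylane for 10 days. The exclusion rule opens "If a patient displays secondary effects or develops an allergy to metronidazole", extends the same condition to Carbosylane, and states that "he/she will be excluded from the study and will be replaced by another patient". No severity threshold is given. Fifty patients are to be recruited "in order to maintain a 20-patient cohort for each experimental arm".

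Other sections bear on the same rule:

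- **3.3** tells patients already on a treatment that affects gut motility or sensitivity to continue it, and adds: "In the event of a significant change during the study, the patient will be excluded".
- **4.1** plans 25 per arm "to compensate for non-compliant patients and patients who develop allergies or intolerance to treatment, or who are lost at follow-up". The base of 20 per arm is declared arbitrary.
- **4.2** fixes the timing of the outcome: "The bowel diaries will be completed at the beginning of the study before the treatments and at the end of the treatments".
- **4.3** says that the change and the percentage decrease in flatus incontinence episodes "will be calculated and will compared between the two groups of patients".
- **7.5** begins its list with "Metronidazole could cause the following serious adverse events: digestive disorders, glossitis". It gives no frequencies and has no matching list for Carbosylane.
- **8.1** describes adverse events on metronidazole as fairly uncommon and usually ending when the drug is stopped.

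**The concern.** The trigger in 3.6 is a reaction to the assigned drug, so the exclusion necessarily comes after randomisation. The change of treatment in 3.3 can also come after it. Both events may depend on which drug was given and on how the patient is doing. The outcome is a bowel symptom, and digestive disorders head the list of metronidazole reactions in 7.5, so a link between exclusion and outcome is plausible.

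Replacement restores the count of 20 per arm but not the comparability that randomisation gave. Section 2 asks whether antibiotic treatment improves flatus incontinence in patients with a positive breath test. Followed as written, the trial would answer this only for patients who tolerated their drug. If more patients are excluded on metronidazole and they would have done badly, metronidazole looks better than it is for a patient starting it. If they would have done well, it looks worse.

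**Working it through.** **The plan's own figure.** Keeping 20 per arm with 25 recruited implies a loss of 5/25 = 20%. Then 20/(1 - 0.20) = 25 per arm and 40/(1 - 0.20) = 50 in total, as stated. The recruitment arithmetic is correct. The 20% is an allowance for all reasons together (non-compliance, intolerance, loss to follow-up), not a side-effect rate and not a cap.

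**What happens to an excluded patient.** The primary outcome needs the end-of-treatment diary (3.6, 4.2). A patient excluded from the study before then has no later visit or diary described anywhere. The natural reading is that no outcome is collected.

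**Illustrative bias in the responder rate (more than 50% reduction).** All rates here are assumptions:

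- Response p among all randomised patients is equal in both arms, at 30%, 40% or 50%.
- The excluded fraction e is 12% (3/25) or 20% (5/25) on metronidazole and 4% (1/25) on Carbosylane.
- Kept rate = p/(1 - e) if the excluded are all non-responders, and (p - e)/(1 - e) if all are responders.

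Example with p = 40% and 12% v 4%:

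- Excluded all non-responders: 0.40/0.88 - 0.40/0.96 = 45.5% - 41.7% = +3.8 points.
- Excluded all responders: 0.28/0.88 - 0.36/0.96 = 31.8% - 37.5% = -5.7 points.

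| Excluded (metronidazole v Carbosylane) | p | Gap, excluded all non-responders | Gap, excluded all responders |
|---|---|---|---|
| 12% v 4% | 30% | +2.8 | -6.6 |
| | 40% | +3.8 | -5.7 |
| | 50% | +4.7 | -4.7 |
| 20% v 4% | 30% | +6.2 | -14.6 |
| | 40% | +8.3 | -12.5 |
| | 50% | +10.4 | -10.4 |

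The gap is 0 if the excluded respond like the rest. It is also 0 if both arms lose the same fraction with the same link to outcome.

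**Illustrative bias in the mean percentage decrease.** Suppose excluded patients do D points worse than kept ones in both arms. The mean over all randomised patients equals the kept mean minus e × D, so with equal true means the spurious gap is (eM - eC) × D, where eM and eC are the excluded fractions on metronidazole and Carbosylane. For D = 20 to 50:

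- 12% v 4%: 0.08 × D = 1.6 to 4.0 points.
- 20% v 4%: 0.16 × D = 3.2 to 8.0 points.

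The sign reverses if excluded patients do better.

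**Scale against sampling error.** The 95% half-width for a difference in response at 20 per arm is 1.96 × √(2p(1 - p)/20), which is 28.4, 30.4 and 31.0 points at p = 30%, 40% and 50%. The illustrative bias is smaller than this, but it is systematic.

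**The case against.** **The missing diary is not stated.** Section 4.2 has every patient complete the diaries and record side effects in them. Because diaries are kept only before and at the end of treatment, on-treatment side effects would mostly be noted in the final one, which suggests that some affected patients complete it. Section 4.1 also speaks of allergy or intolerance, which is narrower than any side effect. This stands as a caution: a reader might infer that these diaries are certainly lost and that no analysis plan could help, but the protocol does not go that far. It does not remove the point, since nothing provides for follow-up of someone already excluded and replaced. An analysis plan can use such outcomes only if they are collected.

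**Section 3.3 has a limited reach.** A reader might infer that a patient who newly starts an anti-diarrhoeal for worsening symptoms is also excluded. The text concerns patients already on such treatment, so that chain is not supported.

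**The rates have no source.** This is right. Section 8.1 points to uncommon adverse events, and 20% on metronidazole would use that arm's whole recruitment allowance on exclusions. A reader might infer from 7.5 that the result is tilted towards metronidazole, but that list gives no frequencies, and the range above runs on both sides of zero.

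**The effect on error rates depends on the test, and the protocol names none.** Take the case where the excluded are all non-responders, with p = 30% to 50% and 20 per arm. The chance of a false result favouring metronidazole at two-sided 5% is:

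| Test | No exclusion | 12% v 4% | 20% v 4% |
|---|---|---|---|
| Uncorrected chi-square | 2.1-2.7% | 3.9-4.3% | 6.3-9.0% |
| Fisher's exact | 1.0-1.2% | 2.0-2.2% | 3.4-5.2% |

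With Fisher's test the milder case stays below the nominal 2.5%.

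**This is a pilot of arbitrary size.** That limits the consequence, but the protocol still compares the groups on its primary outcome, and the estimate may inform later work.

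**Conclusion.** The point holds for the rule itself. The protocol fixes exclusion and replacement after randomisation, triggered by a reaction to the assigned drug, and describes no outcome collection afterwards. The primary comparison would then cover only patients who tolerated their treatment. That reading rests on one inference: that a patient excluded from the study gives no final diary.

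The effect on the result is not established. Bias needs exclusion that differs by arm and is linked to outcome, and the protocol gives no rates for either. Under the assumed rates the shift is about 3 to 10 points in favour of metronidazole or about 5 to 15 points against it, and it can be zero. A reader might infer that harms data are lost as well; they are not, because section 7.4 keeps adverse events in the case report form and the sponsor's register.

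The rule should be changed, because the change is cheap and outcomes that were never collected cannot be recovered later.

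**What to change.** In section 3.6, replace the exclusion sentence with: *A patient with side effects or allergy may stop the study drug but stays in the study, completes the 3-day diary at the end of the planned 10 days, and is analysed in the randomised arm; patients are not replaced and 25 are randomised per arm.*

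In section 3.3, replace the exclusion of patients whose treatment changes with: *The change will be recorded and the patient kept in the study and analysis.*

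The handling of diaries that are still missing, for example after loss to follow-up, can be left to the statistical analysis plan. A comparison of completers should be supportive only.

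**Cost.** One diary from each patient who stops early, and no extra patients: up to 25 per arm are analysed instead of 20. The effect may be diluted if those who stop do badly. For illustration, kept rates of 65% v 25% (40 points) become 0.65 × 0.80 = 52% v 0.25 × 0.96 = 24% (28 points) if 20% and 4% stop and none of them responds. Power with Fisher's test then goes from 61% at 20 per arm to 45% at 25 per arm. If those who stop respond like the rest, it rises to 78%. The protocol plans no power, so these figures only show the trade-off.

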**4. DATA ANALYSIS AND STATISTICS**

**4.1 Number of patients**

Due to the lack of a preliminary study on the efficacy of treatments for flatus incontinence, we were unable to determine a sample size and decided to arbitrarily enroll 20 patients in each group for the pilot study.

To maintain 20 patients in each experimental arm (i.e., 20 patients treated with Carbosylane^®^ and 20 with metronidazole), we plan to recruit 25 patients for each experimental arm to compensate for non-compliant patients and patients who develop allergies or intolerance to treatment, or who are lost at follow-up. The frequency of positive glucose breath tests in patients with flatus incontinence is difficult to estimate because this has never been investigated. However, we presume that one out of three patients will have a positive glucose breath test.

**4.2 Data collection**

**Demographic data, clinical symptoms**: All the data will be collected and will be compiled in individual patient case report forms (CRFs), which will be archived in the investigation center. Information will be collected by the research staff or the investigator from the patient and from his/her medical record.

**Bowel diary**: Three-day bowel diaries describing flatus incontinence episodes (main criterion), bowel movements, urgency episodes, and fecal incontinence episodes will be completed by each patient. The treatment and the secondary effects will be noted in the diaries. The bowel diaries will be completed at the beginning of the study before the treatments and at the end of the treatments.

**Fecal incontinence severity score**: The Cleveland Clinic score will be used (Jorge, 1993). Scores will be recorded at the beginning and at the end of the study.

**Quality of life scores**: Quality of life will be evaluated using two questionnaires that have been validated in French. One is specific for fecal incontinence (FIQL) [Rullier, 2004] while the other is specific for functional digestive disorders (GIQLI) [Slim, 1999]. These questionnaires will be completed at the beginning and at the end of the study.

**Symptom scores**: The patients will be asked to subjectively rate the intensity of each symptom (bloating, abdominal pain, borborygmi) using the following scores: 0 = none, 1 = mild, 2 = moderate, and 3 = severe. The means of the scores attributed daily for 3 days will be calculated to obtain the final scores for the symptoms at the beginning and at the end of the study.

**Treatment compliance**: Treatment compliance will be evaluated by counting the number of tablets remaining at the end of the study.

**4.3 Data analysis**

Results will be expressed as means ± standard deviation. The mean number of flatus incontinence episodes during the 3 days prior to and at the end of the treatment will be calculated. The difference between the mean number of flatus incontinence episodes before and during the treatment and the percentage decrease in the mean daily number of flatus incontinence episodes will be calculated and will compared between the two groups of patients (metronidazole and Carbosylane^®^ groups). The severity scores, quality of life scores, mean number of bowel movements, fecal incontinence episodes, urgency episodes, and symptomatic scores will be compared between the two groups.

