**3. METHODS**

**3.1 Outcome measures**

The main outcome measure will be the daily number of gas leakages.

The secondary endpoints will be:

- The fecal incontinence severity score
- The quality of life scores
- The frequency of fecal incontinence episodes
- The frequency of urgency episodes
- The frequency of bowel movements
- The symptom scores (abdominal pain, borborygmi)

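### The primary percentage decrease has no value at zero baseline and is unstable at low baseline, and neither compared quantity uses the baseline diary as a covariate

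*Protocol*

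**What the plan says.** Section 3.1 of the protocol names a count: "The main outcome measure will be the daily number of gas leakages". Section 3.6 turns it into a relative change: "The main primary outcome will be the percentage decrease in the mean daily number of gas leakages reported in the 3-day diaries", and defines a responder as a patient with a reduction of more than 50%. Section 4.3 compares two quantities between the arms. One is absolute ("The difference between the mean number of flatus incontinence episodes before and during the treatment") and the other relative ("the percentage decrease in the mean daily number of flatus incontinence episodes will be calculated and will compared between the two groups of patients"). The summary is fixed too: "Results will be expressed as means ± standard deviation".

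The baseline diary covers three days and is completed before randomisation (Section 3.6). Sections 3.2 and 3.3 set no minimum number of leakages for entry, and Section 3.4 limits only the accompanying fecal episodes. Section 4.3 names no test, model or covariate and no rule for a zero baseline. On size, Section 4.1 says "we were unable to determine a sample size" and that the investigators "decided to arbitrarily enroll 20 patients in each group for the pilot study".

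**The concern.** A percentage decrease per patient puts a short, noisy count in the denominator. With a zero in the baseline diary the primary outcome has no value. With a one or a two it exists but swings widely. The scale is also lopsided: improvement stops at 100%, while worsening has no limit. A mean and SD are the summaries most exposed to such values.

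The raw difference is defined at zero, but patients with the highest counts dominate it. Neither quantity uses the baseline as a covariate, although every randomised patient should have one. With about 20 patients per arm, the result could turn on a few low-baseline patients, and precision already paid for could be lost.

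The percentage has to be read as a per-patient figure. The responder rule applies it to individuals, and a mean with an SD needs one value per patient.

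**Working it through.** **1. The plan's own figure.** There is no power calculation to reproduce. Section 4.1 says "we plan to recruit 25 patients for each experimental arm" to keep 20. This fits 20/(1 - 0.20) = 25, but the 20% is back-solved and not stated. No alpha, SD, effect or baseline-to-end correlation is given. All such values below are assumptions, with a two-sided alpha of 0.05.

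**2. Instability.** Percentage decrease = 100 × (baseline - end)/baseline. For 1 leak in three days at baseline and 4 at the end, it is 100 × (1 - 4)/1 = -300%. Compared with an unchanged patient (0%), this one value moves a 20-patient arm mean by 300/20 = 15 points.

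**3. Unadjusted change against ANCOVA, normal formula.** With 20 per arm, 80% power needs a difference of (1.960 + 0.842) × √(2/20) = 0.886 SD of the analysed variable. With equal variances at both times and correlation ρ, the change score has variance 2(1 - ρ) and the adjusted end value 1 - ρ². Their ratio is 2/(1 + ρ). With the effect set so that ANCOVA has 80% power:

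| ρ | variance ratio | effective n per arm, of 20 | power of raw change |
|---|---|---|---|
| 0.5 | 1.333 | 15 | 68% |
| 0.7 | 1.176 | 17 | 73% |
| 0.9 | 1.053 | 19 | 78% |

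**4. Skewed counts, simulation.** Assumptions: 20 per arm; log-normal patient rates with log-SD 0.8; log-rates correlated ρ between baseline and end; Poisson counts over 3 days; end rates 80% of baseline in one arm and 40% in the other; 4,000 trials per row (Monte Carlo standard error at most √(0.25/4000) = 0.8 points). The percentage analyses omit zero baselines because no value exists. Log-ANCOVA uses log(count + 0.5) and keeps everyone.

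| leaks/day, ρ | raw difference, t-test | percentage, t-test | percentage, rank test | log-ANCOVA |
|---|---|---|---|---|
| 2, 0.5 | 24.7% | 32.3% | 44.2% | 56.1% |
| 2, 0.7 | 28.6% | 39.8% | 50.6% | 61.2% |
| 2, 0.9 | 38.4% | 50.9% | 61.7% | 66.6% |
| 5, 0.5 | 29.5% | 39.9% | 57.4% | 69.3% |
| 5, 0.7 | 37.6% | 52.8% | 69.0% | 77.1% |
| 5, 0.9 | 53.6% | 73.8% | 87.4% | 88.6% |
| 10, 0.5 | 30.8% | 48.9% | 65.6% | 78.2% |
| 10, 0.7 | 40.2% | 66.6% | 79.2% | 86.5% |
| 10, 0.9 | 60.9% | 90.1% | 96.9% | 97.6% |

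Gain of log-ANCOVA:
- Over the raw difference: 28 to 47 points.
- Over the t-test of percentages: 15 to 29 points in eight rows, and 7.5 in the last (97.6 - 90.1).
- Over the rank test: 1 to 13 points.

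With no treatment effect (ρ = 0.7), log-ANCOVA rejected in 4.8% to 5.3% of trials.

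**5. Zero baselines in the same simulation.** The share of patients is about 6.5% at 2 leaks per day, 1% at 5 and 0.1% at 10. At least one such patient appears among 40 in about 93%, 32% and 6% of trials.

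**6. Another distribution.** Log-normal rates favour a log-scale analysis, so gamma-distributed rates were also tried (means 2, 5 and 10; average end rates again 80% and 40% of baseline; 3,000 trials each). Log-ANCOVA then gained about 21 to 38 points over the raw difference, 6 to 17 over the t-test of percentages and 1 to 8 over the rank test. In some scenarios percentage decrease matched or beat ANCOVA on untransformed counts (for example 52.5% against 46.5%). Zero baselines ranged from 0.4% to 14%.

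**The case against.** The strongest reply is that most of the apparent power loss comes from a t-test the protocol never names. A rank test on the same percentages recovers about half or more of the gap, and nearly all of it at high correlation. A rank test also stops one extreme value from dominating. This stands, and it is why the rank-test column is shown.

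Second, the choice of test, covariates and handling of uncomputable values is commonly left to an SAP, which is not at hand. This stands for the missing covariate, which is silence and not a decision against adjustment. It does not reach the metric. Sections 3.6 and 4.3 fix the percentage, and an SAP could not replace it as primary without departing from the protocol.

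Third, patients referred for flatus incontinence will seldom record three days without a leak. That is fair if typical counts are 5 to 10 per day, but less so near 2.

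A reader might also infer more than the text supports:
- **That the plan forfeits a known share of its power.** It states none. The trial is a pilot of arbitrary size, so no planned figure is contradicted.
- **That zero-baseline patients are silently dropped.** Nothing says so. The protocol gives no rule.
- **That both compared quantities fail at zero.** Only the percentage and the responder rule do.
- **That the counts are known to be skewed.** This is plausible, but assumed here.

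**Conclusion.** The point holds in this limited form and is worth changing. Two parts need no assumption about variability. The primary metric and the responder rule have no value for a patient whom eligibility admits, and at low baseline one patient can shift an arm mean by 15 points.

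The third part, lost precision, is a possibility whose size depends on the scenario. Within the assumptions above it is large against the raw difference, moderate against a t-test of percentages and small to modest against a rank test. Log-ANCOVA was ahead in every scenario run, but all inputs (mean count, spread, correlation, effect) are assumed.

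**What to change.** Make the primary between-arm comparison a model of the end-of-treatment 3-day leakage count with the baseline count as covariate. Either ANCOVA on log(count + constant) or negative-binomial regression with log(baseline + constant) would serve. Only the former was simulated here. Include zero-baseline patients and report the rate ratio with its 95% CI. This also returns to the count that Section 3.1 names. Keep the percentage decrease and the responder rate as secondary or descriptive, state how a zero baseline is handled in each, and show medians and quartiles beside means.

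The cost is about a paragraph in Sections 3.6 and 4.3, with no new data or patients. There are two small drawbacks. A rate ratio is less familiar to clinicians than a percentage decrease, and the added constant must be fixed in advance.
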